|                                         | 
stem cell harvest. After completion of stem cell harvest, subjects will resume protocol treatment.
 
Subjects who complete 24 months of D-KRd will then proceed to lenalidomide single-agent maintenance at least tolerated dose on Days 1-21 in 28-day cycles.
 
All subjects will undergo testing for minimal residual disease (MRD) using next generation sequencing (NGS) using clonoSEQ with 10-6 sensitivity at the end of Cycles 8 and 24. After Cycle 24, testing will continue on a yearly basis for as long as the subject is free of progression for a maximum follow-up period of 2 years. If a CR is suspected after Cycle 8, subjects will undergo MRD testing at Cycle 12 and/or 18 as well.
                                                                                                                                                                                                                                                                                                                                                                                                                                                                                                                                                               |

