### **4 INVESTIGATIONAL PLAN**

#### **4.1 Overview of Study Design and Dosing Regimen**

This study will be a multi-center, open-label, phase 2 study, enrolling subjects with newly diagnosed MM requiring systemic chemotherapy. All dosing schedule is based on 28-day cycles. Subjects will receive treatment until disease progression or unacceptable toxicity (whichever occurs first).

Enrolled subjects will initially receive lenalidomide at 25 mg per dose (see below if previously unable to tolerate 25 mg) on Days 1-21. Carfilzomib will be dosed at 20 mg/m^2 on Days 1 and 2 and 36mg/m^2 thereafter (Days 8,9,15, and16). Alternative escalation will be allowed on Cycle 1 if the treating

investigator considers it necessary as follows: 20 mg/m^2 on Days 1 and 2 escalated to 27 mg/m^2 on Days 8 and 9, and then to 36 mg/m^2 on Days 15 and 16. Daratumumab will be administered by subcutaneous injection, provided as a fixed-dosed of 1800 mg and 30,000 units hyaluronidase per 15 mL (120 mg and 2,000 units/mL) for all cycles. The injection will be given by manual push over 3 to 5 minutes in the abdominal SC tissues in left/right locations, alternating between individual doses. Dexamethasone will be dosed at 40 mg PO per week for subjects < 75 years and 20 mg PO per week for subjects ≥ 75 years during Cycles 1-4. Dose modifications will be mandated based on aggressive schedule of dose modification for toxicities as per specific guidelines. Otherwise, patients will continue at their best tolerated dose of lenalidomide on Days 1-21 and their best tolerated dose of carfilzomib on Days 1, 2, 8, 9, 15, 16 in Cycles 1-4 and Days 1, 2, 15, 16 in Cycles 5-8.

All subjects will have monthly clinic visits for disease assessments. Treatment will continue on protocol for up to 24 months or if carfilzomib, lenalidomide and daratumumab are permanently discontinued. If dexamethasone is discontinued due to toxicity, carfilzomib, lenalidomide and daratumumab may be continued if tolerated without dexamethasone. Toxicity will be graded using the National Cancer Institute Common Terminology Criteria for Adverse Events version 4. Patients who complete 24 cycles will then continue single-agent lenalidomide at best tolerated dose (up to 25 mg) in 28-day cycles. This regimen will continue until there is progression of the disease or the toxicities require discontinuation of the drug.

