### **6.3.2 Lenalidomide Administration**

US: Lenalidomide will be prescribed and obtained commercially in accordance with the Revlimid REMS® program of Celgene Corporation. Per standard Revlimid REMS® requirements, all investigators who prescribe lenalidomide for research subjects enrolled into this trial must be registered and must comply with all requirements of the Revlimid REMS® program. Prescriptions must be filled within 7 days. Only enough lenalidomide for one cycle of therapy will be supplied to the patient each cycle. Unused lenalidomide will be counted and documented by each site. Unused lenalidomide will be returned to Celgene by the site using instructions provided by Celgene.

Subjects will receive lenalidomide as follows in 28-day cycles:

- Cycles 1-24: 25 mg (or best tolerated dose) PO Days 1-21

Lenalidomide should be taken each evening at approximately the same time. Lenalidomide is taken with water on a full or empty stomach. Subjects should not break, chew or open capsules. If possible, late doses of lenalidomide should be taken on the assigned day but should not be made up the next day. Vomited doses will not be made up. Subjects should be instructed to never take lenalidomide past Day 21 of each cycle.

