| Neurological Assessment                       | X                                   |   |   |   |    |    |    |                              | X                                  |   |   |    |    |    | X               |                 |
| Correlative Samples                           |                                     |   |   |   |    |    |    |                              |                                    |   |   |    |    |    | X  |                 |
| Bone marrow aspirate sample for MRD analysis  | X                                   |   |   |   |    |    |    | X                            |                                    |   |   |    |    |    | X               | X  |
| CT-PET                                        | X                                   |   |   |   |    |    |    |                              | X                                  |   |   |    |    |    | X               | X  |
| Adverse Events                                | Ongoing                             |   |   |   |    |    |    |                              |                                    |   |   |    |    |    |                 |                 |
| Concomitant Medications                                    | Ongoing                             |   |   |   |    |    |    |                              |                                    |   |   |    |    |    |                 |                 |
| Daratumumab                                   | X                                   |   |   |   | X  |    |    |                              | X                                  |   |   |    |    |    |                 |                 |

| PROCEDURES                                       | KRd + Dara Consolidation Cycles 5-8 |   |   |   |    |    |    |                              | KRd + Dara Maintenance Cycles 9-24 |   |   |    |    |    | End of Tx | LTFU            |
|--------------------------------------------------|-------------------------------------|---|---|---|----|----|----|------------------------------|------------------------------------|---|---|----|----|----|-----------|-----------------|

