| DAY                                              | 1                                   | 2 | 8 | 9 | 15 | 16 | 22 | End of Cycle 8  | 1                                  | 2 | 8 | 15 | 16 | 22 |           |                 |
| Carfilzomib                         | X                                   | X | X | X | X  | X  |    |                              | X                                  | X |   | X  | X  |    |           |                 |
| Revlimid® (Lenalidomide)         | X                                   | X | X | X | X  | X  |    |                              | X                                  | X | X | X  | X  | X  |           | X  |
| Dexamethasone                       | X                                   |   | X |   | X  |    | X  |                              | X                                  |   | X | X  |    | X  |           |                 |
| Survival and New Cancer Evaluation  |                                     |   |   |   |    |    |    |                              |                                    |   |   |    |    |    |           | X               |

\* Variations of  $\pm 3$  days of the scheduled visit are permitted however doses of carfilzomib may only be rescheduled by up to 2 days (Section 6.3.1).

\*\*The KRd + Dara consolidation cycles are Cycle 5 – 8. Maintenance Cycles are 9-24.

#### Footnotes for Appendix 8

+ Documented informed consent must be obtained within  $\leq 30$  days prior to initiation of therapy.

1. Includes neuropathy history.
2. May be within 30 days planned treatment start. Includes: lateral radiograph of the skull, anteroposterior and lateral views of the spine, and anteroposterior views of the pelvis, ribs, femora, and humeri. Skeletal surveys performed outside of the 30 day window may be considered for inclusion. Please contact the Lead Principal Investigator and/or/CRA on a case-by-case basis. End of treatment skeletal survey only if clinically indicated.
3. 12-lead ECG, including QTc interval. End of treatment ECG only if clinically indicated.
4. For Day 1 of cycle 1, screening results may be used if within 7 days of treatment start.
5. Complete physical exam (including vital signs [systolic and diastolic blood pressure, respiration, pulse, oral temperature], height, weight, calculation of body surface area [BSA]) and ECOG score) required at screening and Day 1 of each cycle.

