21. Peripheral blood and bone marrow aspirate samples collected at screening, end of cycle 8, time of response (to confirm complete response), end-of-treatment visit, and yearly after end of treatment for up to 2 years. Buccal mucosa swab will be collected at screening only.
22. AEs will be collected from the time of signing informed consent. 30 days following the last dose of D-KRD, patients will be considered to be off-study so no toxicities will be recorded following this period. All concomitant medications must be recorded on the concomitant medications case report form from 21 days before Day 1 through 30 days following the last dose of study drugs.
23. Assessment for disease progression in subjects who did not progress during treatment. At least every 3 months (+/- 30 days) for 5 years from safety follow-up visit (which must be 28days (+/- 3 days) post-last study treatment).
24. Lenalidomide must be prescribed through and in compliance with the Revlimid REMS® program of Celgene Corporation. Prescriptions must be filled within 7 days. Consideration should be given to prescribing lenalidomide 5 to 7 days in advance of Day 1 of each cycle to allow time for required patient and prescriber surveys, and drug shipment to patient. Any unused Revlimid® (lenalidomide) should be returned to the patient for disposition in accordance with the Revlimid REMS® program.
25. Cycles 1-8: Days 1, 2, 8, 9, 15 & 16. Cycles 9-24 Days 1, 2, 15 and 16.
26. Daily on Days 1-21 followed by a 7-day rest period every 28 days. On day coinciding with carfilzomib administration, lenalidomide should be taken at least 4 hours after the carfilzomib dose and may be self-administered at home by the subject. On days that carfilzomib is not administered, lenalidomide should be taken at approximately the same time each day.

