27. Days 1, 8, 15 and 22. Dexamethasone is given between 30 minutes and 4 hours before carfilzomib on days they coincide. Dexamethasone will be dosed at 40 mg PO per week during Cycles 1-4 and 20 mg PO per week during Cycles 5-24. Cycles 9-24 represent the D-KRD Maintenance Phase of therapy and the dose of dexamethasone will remain 20 mg on days 1, 8, 15 and 22. For weeks of daratumumab injection, dexamethasone dose is split into two doses: half the dose prior to daratumumab infusion and half the dose the day after. Split weekly dosing for all other days (e.g. 10 mg on Day 1 and 10 mg on Day 2, etc.) is permitted with approval from Lead Principal Investigator. Dexamethasone given on days without carfilzomib (on Days 22 and 23 of Cycles 1-8) may be self-administered by the subject on an outpatient basis. If Day 2 of carfilzomib dosing is delayed (i.e., Day 2, 9, 16) 4 mg of dexamethasone premedication is required to be used prior to second treatment. Missed doses will not be replaced during a cycle. Missed doses of dexamethasone will not be made up. Single-agent lenalidomide maintenance therapy, is recommended using last tolerated dose of lenalidomide for 21 days in 28 day cycles after D-KRD protocol treatment (Cycles 1-24) is completed.
28. Patients will be followed for survival and development of any new cancers, at least every 3 months. Reports of any death should include date of death and specific cause (disease under study or specify other cause).
29. Evaluations at the end of Cycle 8 may be done on Day 1 of the next Cycle 9.

30. Plasmacytoma evaluation is required at screening only and may be completed as physical exam or imaging if indicated and at the treating investigator's discretion. After screening, plasmacytoma evaluation is required only for patients who have no other measurable disease and/or at investigator's discretion.

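### Appendix 8 marks lenalidomide on Day 22 of Cycles 9-24, against Section 6.3.2 and the row's own footnote, and the single-agent dose after Cycle 24 is worded three ways

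*Protocol*

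**What the plan says.** **Dosing days, Cycles 1-24.** Section 6.3.2 gives the schedule as "Cycles 1-24: 25 mg (or best tolerated dose) PO Days 1-21" and adds: "Subjects should be instructed to never take lenalidomide past Day 21 of each cycle". In Appendix 8 the second grid has a row labelled "Revlimid® (Lenalidomide) 26,28". Footnote 26, which that label cites, reads: "Daily on Days 1-21 followed by a 7-day rest period every 28 days". Under the block headed "KRd + Dara Maintenance Cycles 9-24" the row carries an X on Days 1, 2, 8, 15, 16 and 22.

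**Dose after Cycle 24.** Three places set it:
- Synopsis, Treatment Overview: subjects who finish D-KRd will go on to "lenalidomide single-agent maintenance at least tolerated dose on Days 1-21 in 28-day cycles".
- Section 4.1: patients who complete 24 cycles will then continue "single-agent lenalidomide at best tolerated dose (up to 25 mg"), until progression or toxicity.
- Appendix 8, end of footnote 27: single-agent maintenance "is recommended using last tolerated dose of lenalidomide for 21 days in 28 day cycles".

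**Overdose.** The Overdose paragraph, which follows the pregnancy reporting text in Section 8.3.4, counts any oral amount above the dose the protocol specifies, and any dosing more frequent than the protocol schedule. It asks for overdoses to be reported in the case report form.

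**The concern.** Section 6 sends readers to Appendix 8 for an overview of treatment. Carfilzomib and daratumumab both change schedule at Cycle 9. A Day 22 mark for lenalidomide that is absent in Cycles 1-8 and appears at Cycle 9 can therefore be taken for a deliberate change of the same kind. A site that dosed by the grid would be dosing outside Section 6.3.2, and by the protocol's own definition that could count as an overdose on a schedule basis.

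After Cycle 24 no controlling section settles the dose, because the schedule in Section 6.3.2 stops at Cycle 24. With three adjectives in three places, the specified dose against which an oral overdose would be judged is not fixed. With *will* in two places and a recommendation in the third, it is also unclear whether this phase is required. Progression-free survival and yearly MRD, both secondary objectives, continue to be followed during this period.

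**Working it through.** There is no stated figure to reproduce, so the check is a side-by-side reading.

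**1. Is the Day 22 mark really in that cell?** The grid has 8 consolidation columns, 6 maintenance columns, End of Tx and LTFU: 8 + 6 + 1 + 1 = 16. The lenalidomide row has 16 cells. An equal count alone proves little, so the neighbouring rows were read against their own footnotes.

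| Row | Maintenance days marked | Footnote says | Agree? |
|---|---|---|---|
| Carfilzomib | 1, 2, 15, 16 | 1, 2, 15, 16 (fn 25) | Yes |
| Dexamethasone | 1, 8, 15, 22 | 1, 8, 15, 22 (fn 27) | Yes |
| Lenalidomide | 1, 2, 8, 15, 16, 22 | 1-21, then rest (fn 26) | No, on Day 22 |

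The rows directly above and below are correctly aligned, so a column shift is unlikely. Day 22 is blank for lenalidomide in the Cycles 1-4 grid and in the Cycles 5-8 part of the same row.

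**2. Does Day 22 fall outside the permitted days?** A 28-day cycle with dosing on Days 1-21 leaves 28 − 21 = 7 rest days, Days 22-28. Day 22 is the first of them. The block covers 24 − 9 + 1 = 16 cycles. That is the span of the column heading, not an expected number of extra doses.

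**3. Do *least*, *best* and *last* give different doses?** Table 6-3 steps down from 25 mg through 20, 15, 10 and 5 mg to 5 mg every other day. Take a subject reduced 25 → 20 → 15 mg who stays there. The lowest level reached is 15 mg, the most recent is 15 mg, and the highest level still tolerated is 15 mg. All three terms agree.

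They can part only if the dose goes back up. Table 6-8 allows this for lenalidomide in the renal row (prior dose may be reinstated if clearance normalises after 2 cycles) and in the hepatic row. In a renal path of 25 → 10 → 25 mg, the most recent dose is 25 mg and the lowest is 10 mg, so *last* and *least* differ if *least* is read as lowest. The documents do not say how many subjects would follow such a path.

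**4. Required or recommended?** The synopsis and Section 4.1 use *will*; footnote 27 uses *recommended*. These differ in force, not only in style.

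**The case against.** On Day 22, the strongest reply is that the grid is not a dosing calendar. Lenalidomide is taken daily, yet the row marks only a handful of visit days, so it has to be read with footnote 26, which limits it to Days 1-21. The synopsis, Section 4.1 and Section 6.3.2 say the same, and only one cycle's supply is provided at a time. This largely stands. The weight of the text is on one side, and actual Day 22 dosing may be rare. It does not remove the contradiction, because the mark conflicts with the footnote attached to its own row.

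A second reply is that other cells in Appendix 8 look odd. The Cycles 1-4 daratumumab row has no Day 22 mark although Section 6.3.5.1 lists Day 22 for Cycles 1-2, and the Disease Assessment row carries a mark under maintenance Day 22. So a table-reading fault cannot be wholly excluded. That is fair, but the carfilzomib and dexamethasone rows make it unlikely here.

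On the dose, the synopsis itself joins *last* and *best* in one phrase for Cycles 1-24, and *least* is one letter from *last* and may be a slip. Both points stand as plausible. The document does not resolve either of them.

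A reader might infer from the full range of Table 6-3 that the three wordings imply doses several-fold apart. The documents do not support that. The range shows that reductions exist, not that the terms diverge by that amount, and on a step-down ladder they usually coincide.

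**Conclusion.** Both inconsistencies are present in the current text. The Day 22 mark contradicts Section 6.3.2 and footnote 26. The dose after Cycle 24 has three wordings, and its status has two.

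The consequence is inconsistent instructions to sites on dosing days and on the maintenance dose, including uncertainty in applying the overdose definition. The statistical design is untouched: the primary endpoint is assessed at the end of Cycle 8, before the maintenance block and before single-agent lenalidomide.

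Two stronger inferences should not be drawn. The grid does not show that subjects will receive a rest-period dose in 16 cycles, since the footnote and the prose agree on Days 1-21. Nor is an effect on progression-free survival or yearly MRD demonstrated: those outcomes are followed in this period, but nothing in the protocol gives such an effect a size.

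The conclusion assumes that the Appendix 8 table has been read correctly, which the adjacent rows support. It takes no position on which day limit, dose term or status is right. The correction is worth making because these are operative dosing instructions, not because an analysis depends on it.

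**What to change.** Reconcile the Cycles 9-24 lenalidomide row of Appendix 8 with Section 6.3.2 and footnote 26, after confirming the cell in the source table. Reconcile the synopsis, Section 4.1 and footnote 27 to a single statement of the lenalidomide dose after Cycle 24 and of whether that phase is required or recommended, so that the overdose definition has one reference. The investigators must decide the content; this review does not propose it. The cost is one grid cell and three phrases, with no change to sample size, endpoints or analysis.

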### 6.3.3 Dexamethasone Administration

Dexamethasone will be administered between 30 minutes and 4 hours preceding carfilzomib (on days that they coincide), as follows:

Dexamethasone will be administered between 30 minutes and 4 hours preceding carfilzomib and between 1 to 3 hours preceding daratumumab (on days that they coincide), as follows:

- Cycles 1-4: 40 mg PO (subjects < 75 years) or 20 mg PO (subjects ≥ 75 years) per week
- Cycles 5-24: 20 mg PO per week

For weeks of daratumumab injection, dexamethasone dose is split into two doses: half the dose prior to daratumumab infusion and half the dose the day after.

- Split weekly dosing for all other days (e.g. 10 mg on Day 1 and 10 mg on Day 2, etc.) is permitted with approval from Lead Principal Investigator.
- Dexamethasone given on days without carfilzomib (on Days 22 and 23 of Cycles 1-8) may be self-administered by the subject on an outpatient basis.
- If Day 2 of carfilzomib dosing is delayed (i.e., Day 2, 9, 16) 4 mg of dexamethasone premedication is required to be used prior to second treatment. Missed doses will not be replaced during a cycle. Missed doses of dexamethasone will not be made up.

### 6.3.4 Daratumumab IV Administration *(IV administration is discontinued and not available after the approval of version 7 of protocol dated February 20, 2023)*

Daratumumab can be administered by IV infusion or subcutaneous injection as assessed by the treating investigator. Method of daratumumab administration will be patient-specific and based on treating investigator's assessment.

Daratumumab (16 mg/kg) can be administered as an IV infusion. Each subject's dose will be calculated based on the subject's weight at Cycle 1 Day 1 rounded to the nearest kilogram. The dose of daratumumab will remain constant throughout the study, unless the subject's weight changes more than 10% from Cycle 1 Day 1. All infusions will be planned as outpatient visits. On daratumumab infusion days, subjects will receive the following medications 1 hour prior to infusion; however, premedication up to 3 hours before

the dose of daratumumab is permitted:

- oral antipyretics (acetaminophen 650 to 1000 mg)
- oral or intravenous antihistamine (diphenhydramine 25 to 50 mg or equivalent).

Daratumumab IV will be administered as follows:

- Cycle 1: 16 mg/kg weekly **OR** Cycle 1 Day 1: 8 mg/kg Day 2: 8 mg/kg, Day 8, 15, 22: 16 mg/kg
- Cycle 2: 16 mg/kg weekly
- Cycles 3-8: 16 mg/kg IV infusion every 2 weeks
- Cycles 9-24: 16 mg/kg IV infusion Day 1

The dilution volumes, initial infusion rates, and increment for the first, second, and subsequent doses are provided in Table 6-1. The first infusion, cycle 1, with a volume of 1,000 mL, takes approximately 8 hours or with a volume of 500 mL, takes approximately 4 hours; the second and subsequent infusions, with volumes of 500 mL, take approximately 4 hours. The maximum infusion rate for all infusions is 200 mL/hour for cycle 1 and any subjects experiencing a Grade 1 or greater infusion reaction. Beginning cycle 2, subjects without a Grade 1 or greater infusion reaction during cycle 1 may receive daratumumab over 90 minutes. Infuse at a rate so that 20% of the calculated dose is infused over the first 30 minutes (200 mL/hour). If tolerated, infuse the remaining 80% of the dose over 60 minutes (400 mL/hour), resulting in an estimated 90 minute infusion (total volume=500 mL). The supporting company may modify the infusion rates or the pre-infusion medications prospectively based upon the information collected to date from this and other studies.

For all infusions, daratumumab will be prepared in sterile, pyrogen free 0.9% NaCl. Preparation of the infusion bags should be done on the day of the planned infusion. Daratumumab must be administered as an IV infusion given through a well-functioning IV catheter by using an infusion pump. The study drug must be filtered by using an inline filter (0.2 µm) during the infusion. Manuals with detailed descriptions for preparation and administration of daratumumab will be supplied to each pharmacy and site.

As noted in the Schedule of Events, all subjects should have vital signs monitored at the start and end of the infusion. If a subject experiences any significant medical event, then the investigator should assess whether the subject should stay overnight for observation. If the subject has not experienced a significant medical event but is hospitalized overnight only for observation, then the hospitalization should not be reported as a serious adverse event.

Patients with a history of obstructive pulmonary disorders may require additional post-infusion medications to manage respiratory complications. Consider prescribing short- and long-acting bronchodilators and inhaled corticosteroids for patients with obstructive pulmonary disorders.

The supporting company may modify the infusion rates (Table 6-1) prospectively based upon the information collected to date from this and other studies. Additional details for administration times and rates, as well as pre-infusion medications, will be provided in the administration guidelines.

